**Acceptability**

1. Client Satisfaction Questionnaire (CSQ-8), a self-reported scale with 8 items that describes satisfaction with a health service (66);

2. System Usability Scale (SUS) (67): This is a self-report survey that determines whether the intervention is serviceable for its intended purpose. The SUS is a reliable tool for measuring the usability. It consists of a 10 item questionnaire with five response options for respondents; from Strongly agree to Strongly disagree.

## Schedule of Events

| **Procedures** | Screening | Baseline | d-DBT Intervention (8 weeks) | Follow up Visit |
| --- | --- | --- | --- | --- |
| Informed consent | X |  |  |  |
| Inclusion/Exclusion Determination | X |  |  |  |
| SCID for the DSM-5 | X |  |  |  |
| SIPS | X |  |  | X |
| Prevention through Risk Identification, Management and Education Screen-Revised |  | X |  | X |
| Connor-Davidson Resilience Scale |  | X |  | X |
| Brief Difficulties in Emotion Regulation Scale (DERS-16) |  | X |  | X |
| Borderline personality dimensions: BSL-23 |  | X |  | X |
| Calgary Depression Scale for Schizophrenia |  | X |  | X |
| The State-Trait Anxiety Inventory |  | X |  | X |
| Global Functioning: Social and Role Scales |  | X |  | X |
| Timeline Follow Back (TLFB) |  | X |  | X |
| Adolescent Alcohol and Drug Involvement Scale (AADIS) |  | X |  | X |
| The Cannabis Use Disorders Identification Test-Revised (CUDIT-R) |  | X |  | X |
| The Daily Sessions, Frequency, Age of Onset and Quantity of Cannabis Use Inventory (DFAQ-CU) |  | X |  | X |
| Columbia-Suicide Severity Rating Scale |  | X |  | X |
| MATRICS Consensus Cognitive Battery (MCCB) |  | X |  | X |
| d-DBT program |  |  | X |  |
| DBT ways of coping checklist to measure DBT-skills use |  |  |  | X |
| Complete Case Report Forms (CRFs) | X | X | X | X |
| Client Satisfaction Questionnaire |  |  |  | X |
| System Usability Scale (SUS) |  |  |  | X |
| Adverse Event Log | X | X | X | X |
| Qualitative Interview |  |  |  | X |

# STATISTICAL PLAN

## Sample Size and Power for quantitative methods

Prior digital intervention feasibility trials in CHR have found that a minimum of 14 participants is sufficient to determine feasibility(90). The sample size was informed by published literature, which suggests 24-70 participants for pilot trials (83-85). We aim to recruit 60 participants in this 8-week pilot RCT to account for potential dropouts (~20%). The proposed sample size will provide reasonably reliable quantitative estimates for the targeted feasibility measures and preliminary data on clinical efficacy. The margins of error for 95% confidence intervals (CI) are ±8.9% for recruitment rate, ±10.1% for adherence/retention/attrition, and ±8.5% for completeness of outcomes. For Aim 3, the minimum detectable effect size is 0.72 (between-group Cohen’s d) and the margin of error for 95% CI is ±0.57 SD.

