# CLINICAL TRIAL OBJECTIVES

## Specific Aim 1

To adapt an existing, d-DBT intervention for use in young people at CHR for psychosis. **H1:** d-DBT can be clinically adapted and refined in a developmentally appropriate way for virtual use among CHR individuals.

## Specific Aim 2

To evaluate the acceptability of the d-DBT invention and the feasibility of conducting a fully powered randomized controlled trial (RCT) of d-DBT in individuals at CHR for psychosis. **H2:** d-DBT will be acceptable to CHR individuals as demonstrated by qualitative feedback, attendance rates of d-DBT sessions, the Client Satisfaction Questionnaire (CSQ) and the System Usability Scale (SUS). d-DBT for CHR individuals will be feasible as demonstrated by our ability to recruit our desired sample of 60 participants and retain 80% of those recruited by the end of the 8-week study period. Participants’ ability to complete the clinical assessment schedule will also serve as a feasibility indicator.

## Specific Aim 3

To assess the preliminary efficacy of d-DBT in improving functioning and reducing psychiatric comorbidities in individuals at CHR for psychosis in an assessor-masked preliminary RCT clinical trial. **H3**: Individuals with CHR receiving d-DBT will demonstrate enhanced resiliency, reduced depression and anxiety, personality disorder pathology, improved emotional regulation scores, reduced substance use, reduced suicidal ideation, improved functioning and cognitive performance as a result of treatment compared to CHR individuals receiving treatment as usual.

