# CLINICAL TRIAL DESIGN

## Overall Design

This is a multi-methods study employing qualitative and quantitative methods to adapt the d-DBT intervention and test the feasibility, and acceptability of d-DBT in individuals with CHR. d-DBT will first be adapted to CHR individuals in collaboration with a youth advisory group. Then an assessor-masked pilot RCT, where d-DBT will be delivered over 8-weeks, will be conducted. Sixty participants are planned to be enrolled in the RCT, 30 in the d-DBT group and 30 in the treatment as usual group. Participants in the d-DBT group will continue with their standard outpatient care. Outcome measures will be completed at study entry and post-treatment. For the qualitative component of the study, 15 post-intervention semi-structured interviews will be conducted.

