## Outcome Assessments

**Measures/Assessment Tools:** Demographic and medical comorbidity assessments, and current medication use will be gathered at baseline. Measures will be completed at study entry and repeated immediately post-intervention at 8-weeks. Clinician rated assessments will be completed with a trained research assistant. Any changes to medication will be recorded at intervention completion. Psychiatric diagnoses will be confirmed using the Structured Clinical Interview for DSM-5 (SCID-5) and Structured Interview for Psychosis-risk Syndromes (SIPS) at baseline. Clinical assessments will be completed at baseline and 8-weeks.

Primary outcomes:

1. Feasibility outcomes will include recruitment (60 participants), retention, and completeness of modules. Completeness of modules will be assessed using a brief survey after every module and participants will receive weekly virtual check ins to help with trouble shooting and enhance engagement. Participants’ ability to complete the clinical assessment schedule will also serve as a feasibility indicator.
2. Acceptability will be informed by the Client Satisfaction Questionnaire (CSQ-8) (66). Semi-structured interviews at the end of the intervention will also provide feasibility and acceptability data.
3. System Usability Scale (SUS) (67) - assesses whether the intervention is serviceable for its intended purpose. The SUS is a reliable tool for measuring the usability. It consists of a 10-item questionnaire with five response options for respondents; from Strongly agree to Strongly disagree.

Secondary Outcomes:

1. Global Functioning: Social and Role Scales (68).
2. Psychosis spectrum symptoms: SIPS (69); PRIME-Revised (70)
3. Mood and anxiety: The State-Trait Anxiety Inventory (71), Calgary Depression Scale for Schizophrenia (72).
4. Emotion Regulation: Brief Difficulties in Emotion Regulation Scale (DERS-16) (73).
5. Substance Use: Adolescent Alcohol and Drug Involvement Scale The Timeline Follow Back (TLFB) method for measuring quantity of cannabis, alcohol, and tobacco use in the past 7 days (74); The Cannabis Use Disorders Identification Test-Revised (CUDIT-R) (75);Daily Sessions, Frequency, Age of Onset and Quantity of Cannabis Use Inventory (DFAQ-CU) (76)
6. Borderline personality dimensions: BSL-23 (77).
7. Resiliency: Connor-Davidson Resilience Scale; CD-RISC (78).
8. Suicidal ideation: Columbia-Suicide Severity Rating Scale (79).

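### The ±10.1% margin stated for adherence matches all 60 participants, but adherence to d-DBT can be observed in only 30

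*Protocol*

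**What the plan says.** The section on sample size and power for quantitative methods lists margins of error for 95% confidence intervals. One of them covers three quantities together: ±"10.1% for adherence/retention/attrition". Completeness of outcomes has its own margin, ±8.5%. The section gives neither the denominator nor the assumed rate behind any of these margins.

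Overall Design fixes the allocation: "Sixty participants are planned to be enrolled in the RCT, 30 in the d-DBT group and 30 in the treatment as usual group". Specific Aim 2 sets the retention target, which is to "retain 80% of those recruited by the end of the 8-week study period". Outcome Assessments names the primary feasibility measures: "Feasibility outcomes will include recruitment (60 participants), retention, and completeness of modules".

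Treatment Regimen assigns the weekly module to the experimental arm. It uses the word adherence when describing the weekly staff check-ins that support the intervention. Control Group Procedures gives the other arm usual care, with no modules.

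**The concern.** Retention and attrition are defined for everyone randomised, so a denominator of 60 suits them. Adherence to a self-led digital programme is defined only for people who receive the programme. Putting the three under one margin gives adherence the precision of the whole trial, when half of the participants cannot contribute to it.

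This matters because the trial is a feasibility study and module completion is a primary feasibility outcome. Participant Compliance Monitoring itself describes poor engagement as a recognised difficulty in interpreting digital interventions. The listed margins support the protocol's claim that 60 participants will estimate the feasibility measures with fair reliability. For adherence, a reader planning the full trial would expect a tighter interval than the design can give.

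**Working it through.** **Inputs**
- Total sample 60, allocated 30 and 30 (Overall Design).
- Retention target 80% (Specific Aim 2). The expected dropout of about 20% in the sample-size section agrees with it.
- Confidence level 95%, so z = 1.96.
- Adherence rate: not stated. Assumed 80%, because adherence shares one margin with retention; 70% to 90% is shown as a range.

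**Formula.** Half-width for a proportion = 1.96 × √(p(1 − p)/n).

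**Reproducing the stated figure.** With p = 0.80 and n = 60: 1.96 × √(0.16/60) = 10.12%, which matches ±10.1%.

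Another pair also matches: n = 48 (80% of 60) with p = 0.85 gives 10.10%. A rate of 85% appears nowhere in the protocol, so 60 at 80% is the likelier source. Either way, both arms are pooled.

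**Adherence on the d-DBT arm.** With p = 0.80 and n = 30: 1.96 × √(0.16/30) = 14.31%. The Wilson 95% interval for 24 of 30 is 62.7% to 90.5%.

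| Assumed adherence | Margin, n = 30 |
| --- | --- |
| 70% | ±16.4% |
| 75% | ±15.5% |
| 80% | ±14.3% |
| 85% | ±12.8% |
| 90% | ±10.7% |

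If only 24 d-DBT participants supplied data, 80% would give ±16.0%. Under the alternative source, 24 d-DBT completers at 85% would give ±14.3%.

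**Ratio.** √(60/30) = 1.41. The margin for 30 is 41% wider than the stated one; put the other way, the stated one is 29% narrower (1 − 1/1.41).

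**What would rescue ±10.1% with 30 participants.** Solving 1.96 × √(p(1 − p)/30) = 0.101 gives p = 0.913. No adherence rate that high is stated. At 80%, the d-DBT arm alone would need 1.96² × 0.16/0.101² ≈ 60 participants, twice the plan.

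**The case against.** The strongest reply is that adherence here is loose wording. It appears in a slashed label beside retention and attrition, the matching rate is the retention target, and adherence is not itself named among the primary outcomes. On that reading the margin describes staying in the study, and it is correct. This carries some weight, but not enough. Treatment Regimen ties the word to the intervention, and completion of the assessment schedule is a separate indicator, with completeness of outcomes given its own ±8.5%. A reader will therefore take adherence to mean engagement with d-DBT.

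A second reply stands in part. The ±14.3% needs a yes/no measure at 80%, and the protocol states neither. Completion is recorded after each of eight modules, so adherence might be summarised as a mean fraction completed. For a fraction with mean 0.8 the variance cannot exceed 0.16, which makes ±14.3% an upper bound. A standard deviation of about 0.28 (0.101 × √30/1.96) would bring the margin down to ±10.1%. The protocol gives no such standard deviation, and the stated figure is reproduced by the formula for a proportion.

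Three stronger readings are tempting, and the document does not support them:
- **Retention in the d-DBT arm is also misstated.** The target is pooled over all recruited, no by-arm margin is given, and ±10.1% is right for the pooled rate.
- **The precision of the CSQ-8 and SUS is misstated.** No margin is given for either, so there is nothing to contradict.
- **The sample size is undermined.** The number 60 is justified by the pilot-trial literature and an allowance for dropout, not by this margin.

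**Conclusion.** The stated margin is right for overall retention and attrition and wrong for adherence to d-DBT. Taking adherence as a yes/no measure at an assumed 80%, the margin is about ±14.3 percentage points instead of ±10.1. The direction does not depend on the exact rate: anywhere from 70% to 90%, 30 participants give a wider margin than stated. The size does depend on it, so ±14.3% should be read as conditional and not as the one true value.

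Severity is minor to moderate. The protocol sets no numerical adherence threshold or progression rule that uses this margin, the feasibility analysis is mainly descriptive, and conduct and efficacy analysis are unaffected. What needs correcting is the claimed precision of one primary feasibility measure.

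**What to change.** Split the sentence in the sample-size section into two statements:
- ±10.1% for overall retention and attrition (n = 60, rate 80%).
- About ±14.3% for adherence in the d-DBT arm (n = 30), with the assumed rate and the yes/no form of the measure written beside it. If a different rate or summary is intended, state that and recompute.

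Say also that adherence is computed on participants allocated to d-DBT only.

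The cost is wording: one stated figure becomes less favourable. Sample size, allocation and procedures stay as they are.

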## Statistical Methods

Data will be analyzed principally using descriptive statistics to assess rates of recruitment, retention, intervention fidelity, engagement, and treatment response. Distributional characteristics of the outcome measures will be assessed for ceiling and floor effects and rates and patterns of missing values. Exploratory trial outcomes including impact of d-DBT on emotional regulation, psychiatric symptoms and functioning will be analyzed using (generalized) linear mixed-effects models with time (baseline, post-treatment), group (d-DBT vs control), time by treatment interaction as the primary predictor. The model will also include covariates to account for pre-treatment clinical characteristics and/or key demographics. The model form will be determined by the distribution features of the outcomes of interest (e.g, continuous, binary or count-type). The efficacy outcome will be impact of d-DBT on functioning, via the Global Functioning: Social and Role Scales. Our prior work with youth has informed us that functioning is more relevant to them than symptom severity (91). Given the small sample size, appropriate to a feasibility trial, we will also calculate point and confidence estimate of effect sizes (Cohen’s *d*) Effect sizes will help with the estimation of the sample size needed for a larger scale confirmatory randomized control trial in the future. Both ITT analysis and per-protocol/completers-only analysis will be conducted to gain insight of estimated efficacy of different subgroups of participants. Full information maximum likelihood approach will be adopted to deal with missing data under the missing-at-random assumption. Diagnostic analysis will be conducted to evaluate the soundness of the statistical assumptions carried by the methods. While the analytic approach can be seen as too complex for the small sample size, it will offer guidance for the analysis plan of the full-scaled trial.

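### The detectable effect of 0.72 is printed without its basis; at two-sided 5% and 80% power it leaves out the 20% dropout that the ±0.57 SD margin beside it allows for

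*Protocol*

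**What the plan says.** All of the figures are in the Protocol.

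- **Sample size and allocation (Overall Design):** "Sixty participants are planned to be enrolled in the RCT, 30 in the d-DBT group and 30 in the treatment as usual group".
- **Dropout (Sample Size and Power for quantitative methods):** the target of 60 is said to allow for about 20% dropout. Specific Aim 2 sets the matching feasibility target: to "retain 80% of those recruited by the end of the 8-week study period".
- **Aim 3 sensitivity (same sample-size section):** "the minimum detectable effect size is 0.72", expressed as a between-group Cohen's d.
- **Aim 3 precision (same sentence):** "the margin of error for 95% CI is ±0.57 SD".
- **Analysis (Statistical Methods):** mixed-effects models with "time by treatment interaction as the primary predictor" plus covariates. Point and interval estimates of Cohen's d will also be calculated.

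The protocol does not give the alpha, the sidedness, the power or the number of evaluable participants behind 0.72. It also gives no correlation between baseline and week 8.

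**The concern.** A minimum detectable effect has a meaning only together with an alpha, a sidedness, a power and a number analysed. Here it is printed without them, next to a two-sided 95% margin. Most readers will supply two-sided 5% and 80% power. On that reading the two Aim 3 figures do not rest on the same number of participants: the margin allows for dropout and the detectable effect does not.

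What is at stake is how the efficacy result is read. If Aim 3 gives no clear difference, 0.72 suggests that the trial would have had a good chance of showing an effect of that size. With the dropout the protocol itself expects, that chance is about 70%, unless a looser test was meant.

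**Working it through.** **Inputs.** 30 per arm randomised (Overall Design). 20% dropout (Sample Size and Power), so 30 × 0.80 = 24 per arm, 48 in all. Outcome in SD units. Alpha and power are not in the protocol, so they are assumed and varied below.

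**Formulas.** Comparison of two means with n per arm and SD = 1:
- 95% margin = 1.96 × √(2/n)
- detectable effect = (z for alpha + z for power) × √(2/n)

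with √(2/24) = 0.2887 and √(2/30) = 0.2582.

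**Step 1. Reproduce the margin.**
- 24 per arm: 1.96 × 0.2887 = 0.566, which rounds to the stated ±0.57.
- 30 per arm: 1.96 × 0.2582 = 0.506, which does not.

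Under this formula 24 is the only whole number per arm that rounds to 0.57. The margin therefore already allows for the dropout.

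**Step 2. Reproduce 0.72.** More than one set of assumptions gives it.

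| n per arm | Test | Power | Detectable d (normal) | Detectable d (t) |
| --- | --- | --- | --- | --- |
| 30 | two-sided 5% | 80% | 2.802 × 0.2582 = 0.723 | 0.736 |
| 24 | two-sided 5% | 80% | 2.802 × 0.2887 = 0.809 | 0.826 |
| 24 | one-sided 5% | 80% | 2.487 × 0.2887 = 0.718 | 0.729 |
| 24 | two-sided 5% | 70% | 2.484 × 0.2887 = 0.717 | 0.733 |

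At two-sided 5% and 80% power, 0.72 needs all 30 per arm. At 24 per arm it appears only with a one-sided test or with 70% power.

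**Step 3. Power for d = 0.72 at 24 per arm, two-sided 5%.** 0.72 / 0.2887 = 2.494; 2.494 − 1.96 = 0.534; Φ(0.534) = 0.70. The noncentral t gives 0.685.

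**Step 4. Could a different n, SD or baseline correlation reconcile the pair?** If both figures come from the same analysis, any such change scales both by the same factor, so their ratio is fixed by alpha and power alone.
- Two-sided 5%, 80% power: 2.802 / 1.96 = 1.43.
- Stated figures: 0.72 / 0.57 = 1.26. Allowing for rounding, the range is 0.715 / 0.575 = 1.24 to 0.725 / 0.565 = 1.28.
- One-sided 5% at 80% power: 2.487 / 1.96 = 1.27. Two-sided 5% at 70% power: 2.484 / 1.96 = 1.27. Both fit.

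So within one analysis the stated pair fits these weaker standards and does not fit two-sided 5% with 80% power, whatever the number analysed.

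**Step 5. Two different estimators.** With baseline adjustment and an assumed correlation of 0.45, the detectable effect at 24 per arm, two-sided 5% and 80% power, is 0.809 × √(1 − 0.45²) = 0.722. The same adjustment shrinks the margin to 0.566 × √(1 − 0.45²) = 0.505. This route reproduces both printed figures only if 0.72 is adjusted and ±0.57 is not.

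**The case against.** A reader might infer that the two figures contradict each other outright, or that they are shown to rest on different numbers of participants. The documents do not support that. The protocol fixes no alpha, sidedness or power for 0.72, and two ordinary choices put both figures on 24 per arm. The efficacy hypothesis is directional ("Individuals with CHR receiving d-DBT will demonstrate enhanced resiliency, reduced depression and anxiety"), and a one-sided test can sit beside a conventional two-sided interval. The Statistical Methods section also describes two quantities, a covariate-adjusted mixed model and a Cohen's d with its interval, so 0.72 and ±0.57 may not come from the same estimator. All of this stands, and it makes the finding conditional.

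It does not remove the point. None of these readings is written down. A directional hypothesis does not by itself set a one-sided test, and the only interval printed beside 0.72 is a two-sided 95% one. Under each weaker standard, 0.72 is a more modest claim than it appears to be, and the sentence would still need to say so.

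The feasibility margins in the same section do not settle the matter. The ±10.1% fits 80% of 60 but also 85% of 48, and the ±8.5% fits 90% of 48. A mixture of bases is plausible, not proven.

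The objection on importance also largely stands. The 60 came from published guidance on pilot size, the primary outcomes are feasibility, acceptability and usability, and clinical outcomes are called exploratory. The next trial is to be planned from the estimated effect sizes, not from this detectable effect.

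**Conclusion.** The point holds conditionally. The ±0.57 SD margin matches 24 evaluable per arm. At two-sided 5% and 80% power, 0.72 matches 30 per arm with no dropout. The figure at the protocol's own 48 evaluable participants is then 0.81 (normal) or 0.83 (t), with power for 0.72 of about 70% (68.5% by t). This rests on an unadjusted comparison of two means and equal dropout in the two arms. If a one-sided 5% test or 70% power was intended, 0.72 already allows for dropout, and what is missing is the statement of that basis. If the two figures come from different estimators, that is what needs stating.

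The severity is minor to moderate. A reader should not conclude that the trial is too small for its purpose: the detectable effect did not set the sample size, and no analysis or decision rule depends on it.

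**What to change.** Put both Aim 3 figures on 48 evaluable participants, use one method for both, and state the assumptions. For example: *With 24 evaluable participants per arm, two-sided 5% and 80% power, the minimum detectable effect is d = 0.81 and the 95% CI margin is ±0.57 SD (normal approximation).* By the t distribution the pair is 0.83 and ±0.58 (2.013 × 0.2887 = 0.581). The two methods should not be mixed.

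If 0.72 is kept, print its basis beside it: one-sided 5% at 80% power, or two-sided 5% at 70% power, with 24 evaluable per arm. If it comes from a baseline-adjusted analysis, name the estimator behind each figure and give the assumed correlation.

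The cost is one sentence. No participants are added and no analysis changes. The first option makes the stated sensitivity less favourable.
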